# A Challenge-Based Approach to Body Weight–Supported Treadmill Training Poststroke: Protocol for a Randomized Controlled Trial

**DOI:** 10.2196/resprot.9308

**Published:** 2018-05-03

**Keywords:** stroke, rehabilitation, falls, walking, hemiparesis, body weight support treadmill training, balance, robotics, mobility, walking challenges

## Abstract

**Background:**

Body weight support treadmill training protocols in conjunction with other modalities are commonly used to improve poststroke balance and walking function. However, typical body weight support paradigms tend to use consistently stable balance conditions, often with handrail support and or manual assistance.

**Objective:**

In this paper, we describe our study protocol, which involved 2 unique body weight support treadmill training paradigms of similar training intensity that integrated dynamic balance challenges to help improve ambulatory function post stroke. The first paradigm emphasized walking without any handrails or manual assistance, that is, hands-free walking, and served as the control group, whereas the second paradigm incorporated practicing 9 essential challenging mobility skills, akin to environmental barriers encountered during community ambulation along with hands-free walking (ie hands-free + challenge walking).

**Methods:**

We recruited individuals with chronic poststroke hemiparesis and randomized them to either group. Participants trained for 6 weeks on a self-driven, robotic treadmill interface that provided body weight support and a safe gait-training environment. We assessed participants at pre-, mid- and post 6 weeks of intervention-training, with a 6-month follow-up. We hypothesized greater walking improvements in the hands-free + challenge walking group following training because of increased practice opportunity of essential mobility skills along with hands-free walking.

**Results:**

We assessed 77 individuals with chronic hemiparesis, and enrolled and randomized 30 individuals poststroke for our study (hands-free group=19 and hands-free + challenge walking group=20) from June 2012 to January 2015. Data collection along with 6-month follow-up continued until January 2016. Our primary outcome measure is change in comfortable walking speed from pre to post intervention for each group. We will also assess feasibility, adherence, postintervention efficacy, and changes in various exploratory secondary outcome measures. Additionally, we will also assess participant responses to a study survey, conducted at the end of training week, to gauge each group's training experiences.

**Conclusions:**

Our treadmill training paradigms, and study protocol represent advances in standardized approaches to selecting body weight support levels without the necessity for using handrails or manual assistance, while progressively providing dynamic challenges for improving poststroke ambulatory function during rehabilitation.

**Trial Registration:**

ClinicalTrials.gov NCT02787759; https://clinicaltrials.gov/ct2/show/NCT02787759 (Archived by Webcite at http://www.webcitation.org/6yJZCrIea)

## Introduction

### Background

Stroke continues to remain the leading cause of long-term neurological disability in the United States [1]. Although there is heterogeneity in the severity and level of disability post stroke, greater than 80% of all stroke survivors are likely to experience walking deficits due to hemiparesis [2]. Altered hemiparetic motor control causes balance and gait impairments, which result in asymmetric, slow (ie, 0.1 to 0.8 m/s), and inefficient walking patterns [3-5]. Such walking patterns place stroke survivors at a greater fall risk, with ambulatory stroke survivors being twice as likely to experience falls compared with elderly individuals [6,7]. Fear of falling, along with generalized deconditioning, comorbidity burden, and lack of social support and self-confidence, confines stroke survivors to sedentary lifestyles [8]. Such lifestyles limit participation in daily activities and predispose stroke survivors to secondary health conditions that negatively impact their overall quality of life [9].

### Treadmill Based Locomotor Interventions for Poststroke Rehabilitation

Not surprisingly, improving walking function is the most common rehabilitation goal stated by the majority of stroke survivors [10]. Unfortunately, most gait rehabilitation paradigms are limited in their ability to generate transferable training gains, to help improve poststroke community ambulatory function [11]. To promote motor learning and activity-dependent neuroplasticity changes during rehabilitation, increased practice of locomotor skills in different situational contexts is required [12]. However, various factors have been shown to limit context-based task practice and transferable training gains during rehabilitation, such as decreased active participation, low cardiovascular training intensities, lack of dynamic balance challenges, over-reliance on clinician manual assistance, and lack of opportunities for prolonged practice of skills applicable to real-world community ambulation [13,14]. To collectively address these factors and to promote greater opportunity for motor learning during gait rehabilitation, several studies recommend treadmill-based gait training paradigms [15], including the recent American Heart Association (AHA) scientific report for exercise training in stroke survivors [16]. However, most treadmill paradigms, especially those that integrate limb unweighting via body weight support (BWS), have had varying degrees of success over the past few decades, with some studies reporting no significant outcome differences compared with over-ground training approaches [17,18].

### Need for Challenge-Based Body Weight Support Treadmill Training Post Stroke

Most BWS treadmill paradigms also tend to use external supports (ie, safety harnesses, handrails) and/or therapist- or robot-guided movements that may limit stroke survivors from independently training at desired exercise intensities and/or the ability to challenge their dynamic balance [13,19]. In addition, the lack of context in providing training challenges to help balance confidence and walking independence for navigating through common real-world obstacles further limits training gains [20,21]. Given the variability of results with BWS treadmill training, a recent Cochrane review calls for further investigation of BWS training outcomes using task-specific paradigms of greater training intensities, without handrail support in ambulatory stroke survivors [22]. Unfortunately, safety concerns and limitations in technology restrict most BWS paradigms in their ability to provide challenging yet safe dynamic balance tasks, while training at higher intensities to help stroke survivors overcome their fear of falling and improve their walking function [16,23].

Thus, the purpose of our study was to examine 2 unique intent-driven, BWS treadmill training paradigms, of similar cardiovascular intensity that emphasizes different dynamic walking challenges encountered during community ambulation. The first paradigm involved walking without any handrail support or manual assistance (ie, hands-free [HF] walking [control group]), whereas the second paradigm incorporated practicing 9 essential challenging (C) mobility skills along with HF walking (ie, HF+C walking), relevant for navigation through common environmental obstacles/hazards. We designed both paradigms based on current neurorehabilitation [14] and AHA exercise recommendations for stroke survivors [16]. We used a novel, robotic, intent-driven, treadmill walking system [24] to provide BWS and a safe gait training environment for both groups. We were primarily interested in assessing the feasibility and impact of both treadmill training paradigms on poststroke walking performance and community ambulation capacity, respectively. We hypothesized that the HF+C group would demonstrate greater balance and functional gait improvements compared with the HF group due to increased practice opportunity of essential challenging mobility skills [25] along with HF walking.

## Methods

### Study Design

We conducted a 6-week, single-blinded, randomized, and parallel-arm study to examine the effects of 2 intent-driven, BWS treadmill training intervention groups (ie, HF training, and challenge (C) with HF (HF+C) training), on improving balance and functional walking outcomes in community-dwelling chronic stroke survivors, with mild-to-moderate hemiparetic gait impairments.

### Sample Size Estimation and Group Allocation

We used a single-factor repeated measures analysis of covariance (ANCOVA; ie, initial walking speed as a covariate) at 80% power, 2-tail level of significance of .05 (ie, *P<*.05), and an effect size of 0.4 for a gait velocity difference of 0.16 m/s (ie, minimally clinically important difference), to determine our sample size for each group. Our estimated sample size was 16 individuals per group; however, we aimed to recruit 20 participants in each group to account for attrition. Thus, our goal was to recruit a total of 40 individuals with poststroke hemiparesis, over a period of 3 years.

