### Primary Outcome Measure

As change in over-ground CWS is an important, valid, sensitive, and reliable measure of poststroke recovery and walking function [56], we chose difference in CWS between groups, from pre- to posttraining as our primary outcome measure [57,58]. On the basis of our power analysis, we planned to include baseline-walking speed as a covariate, if it was significantly related to CWS at pre- and posttraining.

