## Results

### Total Participants Enrolled in Our Study

We assessed 77 individuals with chronic mild to moderate hemiparesis, and excluded 38 individuals who did not meet our inclusion criteria, from June 2012 to January 2015. We enrolled and randomized a total of 39 individuals post stroke for our study, with 19 participants in the HF group and 20 participants in the HF+C group. Data collection along with 6-month follow-up continued until January 2016. Detailed results of this study will be presented in 2 subsequent manuscripts.

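### The stated 16 per group at 80% power cannot be reproduced from the printed inputs for the between-group primary comparison

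*Protocol article*

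**What the plan says.** **Sizing.** The model and power appear under Sample Size Estimation and Group Allocation, where the authors write: "We used a single-factor repeated measures analysis of covariance (ANCOVA; ie, initial walking speed as a covariate) at 80% power". The error rate is set in the same sentence, "at 80% power, 2-tail level of significance of .05". The assumed effect follows there too: "an effect size of 0.4 for a gait velocity difference of 0.16 m/s". The result: "Our estimated sample size was 16 individuals per group; however, we aimed to recruit 20 participants in each group to account for attrition". The section does not say whether 0.4 is Cohen's f or d. It gives no SD, no baseline-post correlation and no number of measurements.

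**Primary comparison.** Under Primary Outcome Measure: "we chose difference in CWS between groups, from pre- to posttraining as our primary outcome measure". Proposed Statistical Methods tests this by ANCOVA, with baseline CWS as covariate only if it proves significantly related to the change. The hypothesis in the Introduction is also comparative: hands-free plus challenge (HF+C) should do better than hands-free (HF).

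**Abstract.** The Results paragraph words the primary outcome differently: "Our primary outcome measure is change in comfortable walking speed from pre to post intervention for each group". It also reports the number randomised as "enrolled and randomized 30 individuals poststroke for our study (hands-free group=19 and hands-free + challenge walking group=20", whereas the main Results section says "We enrolled and randomized a total of 39 individuals post stroke for our study".

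**The concern.** The article prints what looks like a complete calculation together with its answer, but the answer does not follow from the inputs for the comparison the trial is meant to make. A two-arm pre-post comparison involves both group and time, while the sizing names a single-factor model. The abstract's within-arm wording of the primary outcome adds to the doubt about which question was sized.

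Two readings of the results are at stake. If 80% power for the minimal clinically important difference is taken at face value, a null result may be read as evidence of no benefit when the trial could not reliably have shown one. And because both arms receive active walking training, both may improve. Under the abstract's wording, two within-arm improvements could pass as the primary result, although they say nothing about HF+C against HF.

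**Working it through.** **Inputs from the article.** Power 80%; two-sided alpha .05; effect size 0.4 tied to 0.16 m/s; 16 per group, inflated to 20; randomised 19 (HF) and 20 (HF+C). The inflation is coherent: 16/(1 − 0.20) = 20, so 20% attrition. The 16 itself is the problem.

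**Method.** Two groups, one covariate degree of freedom, standardised difference d:

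- noncentrality δ = d × √(n₁n₂/(n₁+n₂))
- df = n₁ + n₂ − 3
- power = P(|t′(df, δ)| > t(.975, df))

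**Reading A: 0.4 is Cohen's f.** For two equal groups d = 2f = 0.8, so the implied SD is 0.16/0.8 = 0.20 m/s.

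| n per group | δ | df | power |
|---|---|---|---|
| 16/16 | 0.8 × √8 = 2.263 | 29 | 59.0% |
| 19/20 | 0.8 × √(380/39) = 2.497 | 36 | 68.1% |
| 25/25 | 0.8 × √12.5 = 2.828 | 47 | 79.1% |
| 26/26 | 0.8 × √13 = 2.884 | 49 | 80.7% |

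Required: 26 per group. The difference detectable with 80% power at SD 0.20 is 0.205 m/s at 16/16 and 0.184 m/s at 19/20.

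**Reading B: 0.4 is Cohen's d.** The implied SD is 0.16/0.4 = 0.40 m/s. Power is 19.4% at 16/16 and 22.9% at 19/20. Required: 100 per group (δ = 0.4 × √50 = 2.828, power 80.4%).

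One-sided testing does not recover 16 either: it needs 20 to 21 per group under A and 78 under B.

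**Adding a baseline-post correlation r (assumed; none is stated).** If the effect size is on the unadjusted SD, ANCOVA raises it to d/√(1 − r²).

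| Reading | r | adjusted d | power 16/16 | power 19/20 |
|---|---|---|---|---|
| A | 0 | 0.800 | 59% | 68% |
| A | 0.5 | 0.924 | 71% | 80% |
| A | 0.63 | 1.030 | 80% | 88% |
| A | 0.8 | 1.333 | 95% | 98% |
| B | 0.9 | 0.918 | 71% | 80% |

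**Within-group route (a possibility only).** For a one-group pre-post test with f = 0.4 on the unadjusted SD, dz = 0.8/√(2(1 − r)). At an assumed r = 0.5, dz = 0.8 and n = 15 (power 82%; 85% at 16). At r = 0.3 the answer is 20, and at r = 0.7 it is 10. If 0.4 is dz itself, n = 52 and power at 16 is 32%.

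**Randomised total.** 19 + 20 = 39, and 77 assessed − 38 excluded = 39. The abstract's 30 contradicts the group sizes in its own sentence.

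**The case against.** **Power may really be near 80%.** If 0.4 is f on the unadjusted SD, a correlation of 0.5 gives 80% at the 19/20 randomised, and about 0.63 gives 80% at 16/16. A condensed article may leave such inputs to the full protocol. This stands as far as it goes: a reader might infer that true power is 59%, and the article does not establish that. It also does not establish 80%. The correlation is not stated, the metric is not named, and the covariate is used only conditionally, so its gain is not guaranteed.

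**Other between-group routes come near 16.** A repeated-measures between-group factor averaged over four assessments, at f = 0.4 and an assumed correlation of 0.5, gives 79% power at 16 per group. A change-score analysis at an assumed correlation of 0.7 needs 16. Both depend on unstated inputs, and the first averages over time points, which is not the stated primary contrast.

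**The sizing was not necessarily within-group.** A reader might infer from the single-factor wording, and from a size quoted per group, that a one-arm pre-post test was sized. The article does not show this. The route gives 15 rather than 16 and needs an assumed correlation of 0.5. It also sits awkwardly with initial speed as a covariate, which has no ordinary role when baseline is already one of the two measurements. A single factor can equally mean group, and a size per group is the usual way to give n per arm.

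**Methods already define a between-group outcome.** True, so the outcome conflict is confined to one abstract sentence. It still needs correcting.

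**Conclusion.** The point holds in this form: for the between-group ANCOVA on CWS, the printed inputs do not yield 16 per group at 80% power. With no further gain from the covariate they need 26 per group (f) or 100 (d). Power is then 59% or 19% at 16/16, and 68% or 23% at 19/20. Under f on the unadjusted SD, 80% needs a correlation of about 0.63 at 16/16 or 0.5 at 19/20. Under d, even a correlation of 0.9 leaves power at 71% at 16/16.

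These figures are conditional on how 0.4 is read and on the assumed correlation, so no single one of them is the trial's power. How the 16 was obtained remains unknown.

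The abstract and Methods do disagree on whether the primary outcome is within or between groups. The 30 against 39 is a clerical slip.

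**What to change.** - Name the effect-size metric and state the SD (adjusted or unadjusted) and the baseline-post correlation with their source. Redo the calculation for the between-group ANCOVA.
- Restate the power for 0.16 m/s, or the difference detectable with 80% power, at 39 randomised and conditional on those inputs. For example, if the adjusted SD is 0.20 m/s: about 68% power, or a detectable difference of about 0.18 m/s.
- Reword the abstract to match Methods, so that the between-group difference in CWS change is the single primary outcome and within-group changes are descriptive.
- Interpret the primary result through its 95% confidence interval, set against 0.16 m/s.
- Correct the abstract's randomised total from 30 to 39.

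The cost is wording only. Recruitment and follow-up are complete, so the design does not change and no participants are added. The stated power may become less favourable.

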### Study Center

We conducted all study meetings, participant assessments, and training sessions at the University of Alabama at Birmingham (UAB) Locomotor Control and Rehabilitation Robotics Laboratory (Locolab).

### Ethics and Recruitment

We obtained study approval from the UAB Institutional Review Board (IRB protocol no: F120425008). The LocoLab program coordinator recruited study participants from the greater Birmingham area, using the UAB Stroke Registry list and an initial phone-screening form (Multimedia Appendix 1). Screened participants and their caregiver (if necessary) met with the program coordinator, who explained the study protocol in detail. Participants who provided informed consent were then scheduled for their baseline assessments.

### Initial Screening

An experienced physical therapist, blinded to the training interventions, evaluated all consented participants using our study inclusion or exclusion criteria to approve participants for study enrollment (Textboxes 1 and 2).

Study inclusion criteria.Age 19 years and above, community-dwelling, unilateral stroke survivorsHistory of cerebrovascular accident (ie, ischemic or hemorrhagic) confirmed by computed tomography, magnetic resonance imaging, or clinical criteriaAt least 5 months after stroke incidentAble to ambulate at least 14 m with/without an assistive device or the assistance of one person, with a self-selected comfortable walking speed of ≤1.0 m/sAble to demonstrate receptive and expressive communication ability.Primary care physician approval for exercise (obtained via the Health Insurance Portability and Accountability Act, that is, HIPPA-approved guidelines)Willing to provide voluntary informed consent

Study exclusion criteria.Presence of serious or uncontrolled cardiovascular conditionsResting systolic blood pressure >180 mm HgResting diastolic blood pressure >110 mm HgResting heart rate >100 bpmHistory of uncontrolled arrhythmias/angina/syncopePresence of amputations and/or any severe musculoskeletal problems that restrict walking, for example:Recent fractures of the lower limbOpen wounds/abscessUse of spasticity management drug therapies for affected lower limb before participation, for example:Botulinum toxin injection (<4 months earlier)Phenol block injection (<12 months earlier)Intrathecal baclofen or oral baclofen (within the past 30 days)Any cognition involvement impairing ability to follow instructions and/or Mini-Mental State Exam Score <24Past participation in any study examining the effects of long-term body weight support treadmill training in (>4 weeks of training); limb-loaded pedaling or lower extremity strengthening; or enrolled in any ongoing study that evaluates lower extremity functionParticipant was unable to arrange for transportation to the study site for all evaluations and intervention sessionsParticipant planned to move out of the area within 18 from the time of study enrollment

### Robotic Treadmill Interface for Hands-Free Gait Training in Both Groups

Both groups trained on a novel robotic treadmill interface, which consists of a robotic-assistive device, called the KineAssist (KA; HDT Robotics, Salon Ohio, US) [28,29], synced to a Bertec treadmill [30]. The KA has been used in various studies to investigate both poststroke and nonimpaired walking biomechanics under different conditions [28,30-33]. The KA interacts with an individual walking inside it through a pelvic harness that secures their hips and waist through flexible cloth straps (Figure 2). The pelvic harness is attached to the KA’s pelvic mechanism that rests at the height of the individual’s center of mass (COM) and can provide vertical BWS (for a maximum body weight of 350 pounds and maximum height of 6 feet 5 inches). Two bidirectional force transducers at each hip enable the mechanism to sense drops in height and essentially *catch* the individual in the event of a misstep or loss of balance. This feature provides a safe environment and prevents falls during training. In addition, the force transducers and treadmill belt are paired through software to form a “force-velocity relationship”; the transducers sense the net force applied to the pelvic mechanism and send a signal to move the treadmill belt, making it an intent-driven treadmill. Thus, an individual walking inside the interface can control the speed of the treadmill and walk at their self-selected CWS (ie, intent-driven), with or without varying levels of BWS.

**Figure 1 figure1:**
[figure not shown]
Study-flow for both paradigms from initial screening, randomization, and stratification to training (6 weeks) with follow-up at 6-months. *CWS: comfortable walking speed.

**Figure 2 figure2:**
[figure not shown]
Individual poststroke walking in the KineAssist (KA) treadmill interface. The KA interface consists of a pelvic mechanism with 2 bidirectional force transducers and 2 interactive force rings attached to a pelvic harness and synced to Bertec treadmill.

Unlike nonrobotic environments that use motorized treadmills combined with overhead BWS harness systems, with or without handrails/external support [17,34,35], the KA interface eliminates reliance on any external support and offers the user control over their own gait speed through the intent-driven treadmill. When the *safety-catch* feature is triggered, force rings on either arm of the pelvic mechanism (see Figure 2) allow the researcher/therapist to interactively assist the individual back to a standing position by amplifying applied forces to each ring in the vertical direction. Thus, participants learn to address their falls and stumbles inside the interface as “errors” that they can then learn to formulate strategies to prevent, as opposed to developing fears and avoiding walking behaviors that might trigger them. The pelvic mechanism also allows movement of the COM in all 3 planes through 6 degrees of freedom (DOF). Unlocking the DOFs enables the individual to explore their limits of stability, whereas locking the DOF provides external stability for those with poor balance. This feature is unique in comparison with other robotic devices, which offer limited mobility or mobility in only one plane [36]. A trunk harness also secures the individual’s trunk when they walk inside the device and prevents excessive forward lean. The KA requires a short participant setup time (5-10 min) with assistance of only 2 individuals, due to a simple computerized user interface and an easily customizable pelvic mechanism. In comparison, more sophisticated robotic treadmill gait trainer systems or nontreadmill-based robotic exoskeleton systems tend to have a long setup time and require more than 2 individuals to help set up a participant [37-39]. We have previously published details on walking biomechanics in the KA interface and its different modes in another paper [24]. However, for this study, we used 3 distinct modes of the KA treadmill interface with and without varying levels of BWS:

Intent-driven mode: Uses the KA’s force-velocity software relationship, which allows participants to drive the belt at their self-selected CWS.Joystick mode: Enables the researcher/therapist to control (externally) the speed of the treadmill belt using a joystick controller. This mode is similar to a typical motor-driven treadmill; however, the operator is able to impose smooth or abrupt speed transitions via the KA software. We used this mode during HF+C training for speeding up and slowing down tasks.KA software modifications: In either of the aforementioned modes, we used the KA software to create some of the 9 essential challenging mobility for the HF+C group. For example, using the joystick mode, we could additionally program variable speed changes, which abruptly changed the speed of the motorized treadmill belt at random intervals. In another instance, we programmed perturbations that disrupted an individual’s forward progression, while walking in the intent-driven mode.

